#### Secondary outcomes

Secondary objectives focus on potential differences in the outcome variables between the stimulation and sham group regarding changes in the scale of depression (PHQ-9 (Patient Health Questionnaire according to Kroenke et al. [55]), generalized anxiety disorders (GAD-7 (Generalized Anxiety Disorders according to Spitzer et al. [56])), severity of somatic symptoms (PHQ-15 (according to Kroenke et al. [57]), and the oral health-related quality of life (OHIP-G14 (Oral Health Impact Profile G14 according to John et al. [58])). Furthermore, changes in clinical parameters (effect of taVNS on the mandibular range-of-motion capacity (Jaw-Motion-Analyzer, Zebris Medical, Isny/Allgäu, Germany), the electromyographic activity of the main chewing muscles (EMG/WinJaw measuring system (Zebris Medical) of masseter muscle, temporalis anterior muscle) [59–61] and the clinical signs of TMD (DC/TMD examination [46]) will be measured. All examinations will be performed at baseline, after 4 weeks of taVNS treatment and after a further 4 weeks without treatment. It will be assessed, if both subjective and objective impairments can be improved and whether the observed effects last 4 weeks without stimulation.

### Treatment groups

#### Stimulation group

The tVNS-L system is manufactured by tVNS GmbH, Erlangen, Germany, and is CE-certified for left-sided transcutaneous auricular vagus nerve stimulation. Both frequency of 25 Hz and pulse width of 250 µs are fixed and applied within a 28-s on/32-s off protocol. The stimulation intensity can be adjusted by the patient. The system is available on the internet and can be bought in the manufacturer’s online shop without prescription. The stimulation will be performed at the tragus of the left ear in accordance with the CE certificate, and the stimulation intensity is adjusted by the patient just above the perception threshold. Stimulation should be performed throughout the day for 4 h.

#### Sham group

In the sham group, a non-connected fake electrode (sham) with an identical appearance as the real electrode is used for stimulation. At the first visit, the stimulation system is demonstrated to the patient with a functional electrode, and the stimulation is adjusted right above the threshold. Then, the intensity is reduced below the threshold, and the patient is instructed to keep the intensity on that level without altering it during the study. However, the patient will then receive a non-functional electrode which ensures that no stimulation is applied to the ear. Hence, the patient will be blinded, while the dentist knows the allocation.

### Study plan

Patients with TMD conditions are routinely screened with different questionnaires and examination procedures at the Department of Prosthodontics of the University Medical Center Düsseldorf. If a chronical TMD is detected (Grade III or IV of the Graduation of Chronic Pain Scale (GCPS) according to von Korff [44]), the patient could be eligible to participate (inclusion/exclusion criteria), is informed about the study, and receives a study information flyer. If the patient is willing to participate, he/she gets an appointment for the initial visit.

#### Visit 0

At the initial visit, the patient will firstly sign the informed consent and is allocated to a group. Then the questionnaires (GCPS according to Von Korff, PHQ-9, GAD-7, PHQ-15, OHIP-G14) will be filled out by the patient, and the examination according to DC/TMD will be performed. Measurements of the mandibular mobility (range-of-motion) and muscle activity will be performed. Afterwards, the patient will receive the stimulator tVNS-L® and receives a brief training and introduction, then the app is installed on the patient’s smartphone. Finally, he/she is advised to contact the principal investigator if any side effects occur. The stimulation phase for 4 weeks starts. After 1 week, the patient will be contacted by one of the examiners to ensure that no further questions or problems occur during the first days of application.

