**Fig. 2 Fig2:**
[figure not shown]
Study periods

**Table 1 Tab1:** Schedule of enrolment, interventions, and assessments

	Study Period			
	Enrolment	Allocation	Post-Allocation	Close-out
TimePoint	-t1	Visit 0	Visit 1	Visit 2
Enrolment				
Eligibility screen	x			
Informed consent	x			
Questionnaires		x	x	x
DC/TMD examination	x	x	x	x
Kinematics		x	x	x
EMG (Electromyography)		x	x	x
Allocation		x		
Installation of digital protocol app on smartphone		x		
Interventions:				
Stimulation				
Sham-Stimulation				
Assessments:				
Download stimulation diary from smartphone app			x	
Baseline questionnaire		x		
Baseline DC/TMD examination	x	x		
Baseline EMG		x		
Baseline Kinematics		x		
Outcome questionnaires			x	x
Outcome DC/TMD examination			x	x
Outcome EMG			x	x
Outcome kinematics			x	x

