### Patients

Patients (≥ 18 years) currently treated for chronic TMD conditions (Grade III or IV of the Graduation of Chronic Pain Scale (GCPS) according to von Korff [44]) at the Department of Prosthodontics of the University Medical Center Düsseldorf will be asked to join the study. A certified dentist with experience in TMD diagnosis will perform the examinations according to the diagnostic criteria for TMDs (DC/TMD) [45, 46]. This study is designed as a single-blinded, double-arm randomized controlled trial (RCT) in a 1:1 allocation ratio as a sham and stimulation group will be compared. A concealed randomization and single blinding will be carried out.

Patients are assigned to one of the two parallel treatment groups using a randomization list, which is based on a random, computer-generated numerical sequence. At the first visit, participants will be assigned to their respective group by a researcher who is not involved in patient recruitment.

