## Discussion

The strength of this protocol is the novelty of investigating taVNS as a potential, well-tolerated, and safe treatment option [33] for patients with chronic TMD symptoms. Further advantages of taVNS are that it can be combined with other treatment options, like splint-, physical- or pharmacotherapy, without risking adverse side effects. Moreover, due to its ear pod-style design, patients may continue their routine activities, facilitating a high treatment compliance [38].

Several studies are available in which healthy participants were subjected to an acute taVNS. Importantly, none of the studies reported an occurrence of relevant side effects in the short or longer run [34, 39, 62, 63]. Only nausea, skin irritation of the ear, and worsening of preexisting tinnitus were observed. The drop-out rate associated with side effects was only 2.6% [64–66].

Due to the complexity of the etiology, the diagnosis and treatment of TMD remain a challenge [21]. A high vagal activity has been considered to improve the psychological health and is hypothesized to have therapeutic potential in a wider spectrum of illnesses [34, 43]. Since vagus nerve stimulation has already been investigated successfully for several other acute and chronic pain disorders with similarities in the pathophysiology of TMD, including migraine, depression, tinnitus, and fibromyalgia [39], a response to the innovative and gentle therapy option of taVNS is possible. Potentially, taVNS could also give chronic TMD pain patients a significant gain in their quality of life, which makes its non-invasive application justifiable.

Potential limitations of the present study include that the taVNS requires the active patient cooperation compared to an implantable VNS [35]. However, due to the practical design of taVNS and the high level of suffering of TMD patients, the patients’ compliance should be high. A further limitation is the single-blinded study design. A future definitive trial should be double-blinded with an independent dentist performing the device instructions and blinded outcome assessors. Furthermore, results will only reflect short- or mid-term effects as the treatment duration will be only 4 weeks [40]. Future studies should also investigate long-term effects.

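### At Visit 0 allocation comes before the baseline measurements and the dentist is unblinded, so the baseline for the between-arm efficacy analyses is not protected from knowledge of the arm

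*Protocol article*

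**What the plan says.** The Visit 0 text in Study plan sets a sequence. After consent and allocation ("the patient will firstly sign the informed consent and is allocated to a group. Then the questionnaires") come the DC/TMD examination and the instrumented measurements, and then the device: "Measurements of the mandibular mobility (range-of-motion) and muscle activity will be performed. Afterwards, the patient will receive the stimulator".

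On blinding, the Sham group section says that "the patient will be blinded, while the dentist knows the allocation". The Patients section has a certified dentist carry out the DC/TMD examinations. It also says that "participants will be assigned to their respective group by a researcher who is not involved in patient recruitment".

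Table 1 puts allocation and the baseline questionnaires, kinematics and EMG in the same Visit 0 column, so it does not set their order. For those three groups of measures Visit 0 is the only baseline. The row "Baseline DC/TMD examination" is marked twice, at enrolment (−t1) and at Visit 0. Table 1 puts informed consent at −t1, whereas the Visit 0 text puts it at Visit 0.

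Data analysis uses Visit 0 in two ways: as a level of the time factor in the 2 × 3 mixed ANOVA, and as a baseline fixed effect in the model described at the end of that section.

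**The concern.** Randomisation makes the arms comparable on what is measured before the arm is known. A baseline recorded afterwards, by someone who may know the arm, loses that guarantee. An examiner who expects one arm to improve may, without intending it, grade palpation pain or opening differently at the start. That difference then appears as a difference in change even if the treatment does nothing.

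The efficacy comparison rests on change from Visit 0 through the group × time interaction, with 10 patients per arm. The allocating researcher's independence protects entry to the trial. It does not protect measurements taken after the assignment has been made.

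**Working it through.** **1. Order and knowledge of the arm.**
- Visit 0 text: consent, allocation, questionnaires, DC/TMD, mobility and muscle activity, device.
- Sham group section: the dentist knows the arm. When the dentist learns it is not stated.
- Patients section: a dentist examines; another person allocates.
- No section requires the baseline to be complete before the arm is revealed.

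Knowledge of the arm during the baseline examination is therefore possible and not excluded. It is not stated as a fact.

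**2. Which baselines are exposed.**

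| Measure | Recorded by | Baseline before allocation? | Exposure |
|---|---|---|---|
| DC/TMD | dentist | yes, at −t1, but repeated at Visit 0 with no statement of which is analysed | direct |
| Range of motion, EMG | measuring systems | no | lesser |
| GCPS | blinded patient | grade known from screening; the Visit 0 score is not | indirect |
| PHQ-9, GAD-7, PHQ-15, OHIP-G14 | blinded patient | none in Table 1 | indirect |
| Recruitment, retention, adverse events, compliance | logs and counts | no clinical baseline used | none |

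**3. The plan's own figure.** The point contests no number, but the sample size was reproduced first to fix the test. Inputs from the section on primary outcomes: alpha 0.05, power 0.95, r = 0.5, 2 groups, 3 visits. Assumed: f = 0.40 for a large effect, and sphericity. With λ = N·m·f²/(1 − r), df1 = 2 and df2 = 2(N − 2), N = 18 gives λ = 18 × 3 × 0.16/0.5 = 17.28 and power 0.953. N = 16 gives 0.924, so 18 is the smallest even N. Then 18/(1 − 0.10) = 20. The stated figures hold.

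**4. Pass-through of a baseline shift.** Suppose one arm's Visit 0 mean is shifted by b SD and there is no true effect.
- Change from baseline: bias = b in size, because change subtracts baseline with slope 1.
- Adjusted for baseline: bias ≈ r·b, so 0.5·b at the planned r.

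**5. Effect on the interaction test.** The article gives no b, so a range is assumed. With n = 10 per arm and r = 0.5, the shift alone gives the interaction a noncentrality of n·b²/[3(1 − r)] = 10·b²/1.5 on 2 and 36 df. A simulation of the 2 × 3 mixed ANOVA under no true effect (40,000 runs per row) gave:

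| Assumed b (SD) | Bias in change (SD) | Bias after adjustment (SD) | Noncentrality | False-positive rate |
|---|---|---|---|---|
| 0 | 0 | 0 | 0 | 5.0% |
| 0.2 | 0.20 | 0.10 | 0.27 | 7.0% |
| 0.3 | 0.30 | 0.15 | 0.60 | 9.3% |
| 0.5 | 0.50 | 0.25 | 1.67 | 18% |
| 0.8 | 0.80 | 0.40 | 4.27 | 41% |

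The noncentral F formula agrees with the simulated rates to within about 0.2 percentage points. The table shows what a shift would do; it is no evidence that one will occur.

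**The case against.** The case on the other side is substantial, and most of it narrows the point.

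- *Some baseline information precedes allocation.* Table 1 has a DC/TMD examination and the eligibility screen at −t1, and the GCPS grade is found at routine screening. A reader might infer that nothing is measured before allocation. That is not so.
- *Many outcomes are untouched.* A reader might infer that every analysis is compromised. The progression indicators in Table 2 (recruitment, retention, compliance) use no clinical baseline, and feasibility is the trial's main purpose.
- *The primary efficacy measure is among the least exposed.* Patients fill in the GCPS themselves, are blinded, and do so before they receive the stimulator. Motion and EMG come from measuring systems.
- *The dentist may not yet know.* A reader might infer that the examiner does know the arm at baseline. The statement about the dentist stands in the account of the sham electrode, which is handed over after the measurements. This stands, and limits the point to missing protection.
- *Ineligibility found after randomisation.* Because DC/TMD diagnoses enter the exclusion criteria and occurrence of an exclusion criterion is an abort criterion, a reader might infer that the repeat examination will remove randomised patients. That is possible, and each would be 1/10 of an arm. But screening is placed at −t1, and nothing says the Visit 0 examination decides eligibility again.
- *The limitation is disclosed.* The Discussion says that "A future definitive trial should be double-blinded with an independent dentist performing the device instructions and blinded outcome assessors". This covers unblinded assessment in general. It does not mention allocation before baseline, which can be corrected even with an unblinded dentist.

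None of these arguments shows that the plan protects the Visit 0 baseline from the allocation.

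**Conclusion.** The point holds in limited form. As written, the Visit 0 order leaves the baseline of the between-arm efficacy analyses open to influence by the arm: mainly DC/TMD, to a lesser degree range of motion and EMG, and only indirectly the self-completed questionnaires. Feasibility and compliance results are not affected.

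A shift of b SD would bias the change estimate by b and a baseline-adjusted estimate by about 0.5·b at r = 0.5. The size of b is unknown, and the 0.2 to 0.8 SD used above are assumptions. The false-positive rates further assume 10 analysed patients per arm, sphericity and a shift at Visit 0 only.

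The two entries for the baseline DC/TMD examination and the two times given for consent are inconsistencies of documentation. They need to be resolved but are not evidence of bias. The sample size is not in question.

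**What to change.** Rewrite the Visit 0 paragraph in this order:

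1. Confirm consent and eligibility.
2. Complete and lock all baseline questionnaires, the DC/TMD examination, mandibular mobility and EMG.
3. Only then does the independent researcher reveal the allocation.
4. Hand over the device and give the training.

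In addition, state whether the −t1 or the Visit 0 DC/TMD examination is the analysis baseline, and make Table 1 and the Visit 0 text agree on when consent is signed.

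The cost is a change of wording and of sequence within one visit. Visit, staff, procedures and sample size stay the same. The reorder protects the baseline only: examiner bias at Visits 1 and 2 remains, as part of the single-blind limitation that the Discussion already discloses.

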#### Four-week stimulation phase

##### Visit 1 (after 4 weeks)

At the first visit, the patient will fill out the questionnaires again (GCPS according to Von Korff, PHQ-9, GAD-7, PHQ-15, OHIP-G14). The DC/TMD examination and the acquisition of the mandibular mobility (range-of-motion) and muscle activity by the appropriate measurement systems will be performed again. Under the patient’s supervision, the stimulation statistics are exported from the smartphone app, and the stimulator is given back to the examiner.

##### Visit 2 (after another 4 weeks)

The last visit will be another 4 weeks later. In this follow-up phase, it should be investigated whether the effect of taVNS is sustained or rapidly washed out in order to evaluate the longer-term therapy success. At the last visit, patients will answer the questionnaires (GCPS according to Von Korff, PHQ-9, GAD-7, PHQ-15, OHIP-G14) for the third time, and the DC/TMD examination, the measurements of mandibular mobility (range-of-motion) and muscle activity will also be performed again.

### End of study

#### Data analysis

This trial features a 2 × 3 factorial design with the factors group (stimulation, sham) and time (Visits 0, 1, 2). Main and interaction effects on the secondary endpoints will be statistically tested via a mixed-measures ANOVA. In case the preconditions for ANOVA use are not met, nonparametric alternatives will be employed. Global effects will be further elucidated by appropriate post hoc comparisons between individual conditions (i.e., per group or time point). The significance threshold will be set to *p* < 0.05, corrected for multiple comparisons where needed. Furthermore, estimates of treatment effect size and confidence intervals will be reported in addition to significance testing results. These analyses will provide a treatment effect estimate on each outcome measure. Outcome measures at baseline, 4 and 8 weeks post-intervention will be entered into the model as the dependent variables with fixed effects of study arm, baseline outcome measures, time, and time point by study arm interaction.

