### Outcomes

#### Primary outcomes

The primary outcomes will be feasibility, compliance, and the determination of clinically relevant taVNS treatment effects. Feasibility will include recruitment and retention rates, randomization success, blind-success, compliance with questionnaires and assessment procedures and the occurrence of any adverse events (Table 2). The compliance of 4 h/day taVNS will be electronically logged by an app on the patient’s smartphone. Treatment is considered to be compliant when at least 80% of patients use the stimulator for at least 2 h (mean) per day. Furthermore, this study was designed to detect clinically relevant treatment effects, which we consider to correspond to statistically large effects according to Cohen [47]. An established and widely used, validated questionnaire will be applied to assess the pain severity and activity limitations (GCPS (Graduation of Chronic Pain according to Von Korff [44])).

**Table 2 Tab2:** Key feasibility indicators for progression [48, 49]

Key indicator	Go—proceed with RCT	Amend—proceed with changes	Stop—do not proceed unless changes are possible
**Recruitment rate** *Target figure: 20 participants*	≥ 70% of target number	51–69% of target number	≤ 50% of target number
**Retention rate** *75% of the participants randomized to intervention group will complete outcome measures T0, T1, and T2*	≥ 70% of target number	51–69% of target number	≤ 50% of target number
**Compliance**	≥ 80% of target number use the stimulator for at least 2 h (mean) per day	61–79% of target number use the stimulator for at least 2 h (mean) per day	≤ 60% of target number use the stimulator for at least 2 h (mean) per day

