According to power calculations done with G*Power 3.1.9.7 and assuming an alpha error level of 5%, a power of 95%, and a moderate correlation among repeated measures (*r* ≥ 0.5), a sample size of *n* = 18 is required to detect significant intervention (stimulation vs. sham) × time (visit 0, visit 1, visit 2) interaction effects of this size. Assuming a drop-out rate of approximately 10%, a sample of *n* = 20 participants will be initially recruited, 10 in each of the two groups “sham” and “stimulation.” Another just-conducted pilot trial on a taVNS intervention also reaches clinically relevant effects with a similarly small sample size [50]. Furthermore, an investigation of taVNS application in fatigue syndrome reported highly significant effects (*p* < 0.0003) with a sample size of *n* = 15 [51]. Other studies evaluating taVNS application in migraine also used samples of 20 to 30 patients [52–54]. Consequently, a sample size of *n* = 20 appears to be sufficient to achieve statistical significance for clinically relevant (i.e., large) effects of taVNS and was therefore adopted in this study.

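### Read literally, the three-visit mixed ANOVA for the secondary endpoints drops a patient's measured Visit 1 result if Visit 2 is missed, and the model described after it does not settle the matter

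*Protocol article*

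**What the plan says.** All references are to the protocol article.

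- **Data analysis.** The design is two groups by three visits. Main and interaction effects on the secondary endpoints "will be statistically tested via a mixed-measures ANOVA", with nonparametric alternatives if its preconditions fail and post hoc comparisons by group or time point. The last sentence describes a model whose dependent variables are the outcomes at baseline, 4 and 8 weeks and whose fixed effects are arm, baseline value, time and arm-by-time. It does not say whether this is the same ANOVA or another method. It names no random effect, covariance structure or likelihood fit.
- **Primary outcomes, sample size.** The calculation assumes "a moderate correlation among repeated measures" of at least 0.5, and "a sample size of *n* = 18 is required to detect significant intervention" by time interactions. Then: "Assuming a drop-out rate of approximately 10%, a sample of" 20 is recruited, 10 per arm.
- **Primary outcomes, Table 2.** The retention indicator reads "75% of the participants randomized to intervention group will complete outcome measures T0, T1, and T2".
- **Secondary outcomes; Visit 1; Visit 2.** Visit 1 follows four weeks of stimulation and the device is handed back there. Visit 2 follows four further weeks without treatment.

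**The concern.** A classical repeated-measures ANOVA needs a complete row for each patient. Visit 1 is the only assessment at the end of treatment. Under the named test, missing a follow-up visit four weeks after the device was returned would remove the patient from the end-of-treatment comparison as well, although that outcome was measured. With 10 patients per arm, each loss counts.

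Two things are at stake. The first is discarded data. The second is bias, if the patients who miss Visit 2 differ in response from those who return and do so differently in the two arms. The trial is meant to inform a larger RCT, so a distorted effect estimate would be carried forward.

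**Working it through.** **1. Sample size reproduced.** Inputs from Primary outcomes: alpha 5%, power 95%, r = 0.5 (the lower limit stated), 2 groups, 3 visits. The effect is described only as large in Cohen's sense; I assume f = 0.40. For the interaction test:

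- λ = N·m·f²/(1 − r) = 18 × 3 × 0.16 / 0.5 = 17.28
- df1 = (2 − 1)(3 − 1) = 2; df2 = (18 − 2)(3 − 1) = 32
- Power is 0.953 at N = 18 and 0.940 at N = 17, so 18 is the smallest N. Then 18/0.90 = 20.

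Both figures reproduce.

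**2. Is the harm mainly loss of power?** No. With 18 completers (10% loss) power is 0.953. Even with 15 (25% loss over the whole trial) it is 0.903.

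**3. Bias among completers.** Assumptions: 10 per arm, SD 1, equal correlation 0.5 between visits, a true effect of 0 or 0.8 SD at both later visits, and 2 of 20 patients lost after Visit 1. Positive errors favour taVNS. Simulated with 4,000 trials per case (8,000 for the last two rows):

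| Who misses Visit 2 | True effect (SD) | Error at Visit 1 (SD) | Error at Visit 2 (SD) |
|---|---|---|---|
| One at random in each arm | 0 or 0.8 | within 0.01 | within 0.01 |
| The poorest responder in each arm | 0 or 0.8 | within 0.01 | within 0.01 |
| The 2 poorest responders, stimulation arm only | 0 | +0.32 | +0.16 |
| The same | 0.8 | +0.32 | +0.15 |
| The 2 poorest responders of all 20 | 0 | 0.00 | 0.01 |
| The same | 0.8 | −0.20 | −0.10 |

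A separate simulation of the last row gave −0.19 at Visit 1.

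**4. Hand check of the one-arm case.** The change from Visit 0 to Visit 1 has variance 2(1 − 0.5) = 1. The two largest of ten standard normal values have expectations 1.539 and 1.001. Removing them shifts the mean of the other eight by (1.539 + 1.001)/8 = 0.32 SD. The slope of the Visit 2 change on the Visit 1 change is (1 − 0.5)/1 = 0.5, giving 0.16 SD at Visit 2. Both agree with the table.

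**5. Keeping the observed data.** The Visit 1 difference using everyone who attended Visit 1 was unbiased in every case. In the one-arm case, a Visit 2 estimate that uses the earlier visits of the patients who left was within 0.02 SD of the truth. There, leaving depended only on observed values.

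**The case against.** The strongest reply is that nothing in the article says completers only. How incomplete patients are handled is normally left to the full protocol or analysis plan, so its absence here is not an error. The closing sentence of Data analysis resembles a linear mixed model, which would keep incomplete patients if fitted by likelihood. Nothing limits a post hoc Visit 1 comparison to patients who also attended Visit 2.

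Much of this stands. The point is not that a missing-data section is absent. It is that a test is named which, taken literally, needs all three visits, and that the sentence which might rescue it is not tied to that test and has baseline on both sides of the model.

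Four stronger readings are tempting, and the document does not support them:

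- **That the sample size shows an intention to analyse completers.** Raising 18 to 20 for 10% drop-out is standard whatever analysis follows.
- **That 25% of the trial is expected to be lost.** The 75% in Table 2 is a progression indicator for the intervention arm. The only drop-out assumed is about 10%.
- **That the analysis will overstate taVNS and raise the false-positive rate.** With 2 stimulation patients lost and no true effect, rejection does rise to roughly 8–11%. That requires all response-related loss to fall in one arm. Patients are blinded, so lack of benefit could equally keep sham patients away. When the 2 poorest responders leave from either arm, rejection under no effect is 4.9% and a real effect is understated.
- **That the primary GCPS analysis is affected.** The ANOVA is named for the secondary endpoints. The power calculation uses the same interaction, but the GCPS test is not expressly tied to it.

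**Conclusion.** The concern holds in a limited form. The test named for the secondary endpoints, in its classical form, discards the measured Visit 1 outcome of anyone who misses Visit 2, and the section describes a second model without reconciling the two.

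At the assumed 10% loss, the consequence for the Visit 1 comparison ranges from no bias (random loss, or the same pattern and number in each arm), through an overstatement of about 0.3 SD (poorest responders leave the stimulation arm only), to an understatement of about 0.2 SD (poorest responders leave from either arm, true effect 0.8 SD). Neither the direction nor the occurrence of bias can be predicted from the document.

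These sizes rest on r = 0.5 between all visits, 10 per arm, and loss driven entirely by the observed change to Visit 1. Weaker dependence gives smaller bias: 0.23 SD instead of 0.31 SD in the one-arm, no-effect case when noise of 1 SD was added to the drop-out rule. The change is worth making because it is cheap and keeps data already collected. It does not show that the trial is invalid.

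**What to change.** In Data analysis, state one model in place of the two descriptions: a likelihood-based linear mixed model for repeated measures, on all randomised patients as allocated, using every available visit. Enter baseline either as a response or as a covariate, not both. Use a small-sample degrees-of-freedom correction (Kenward-Roger is one option). The between-arm contrast at Visit 1 then includes everyone who attended Visit 1.

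The cost is wording and standard software, with no extra patients or measurements. The small downside is reliance on a missing-at-random assumption, which is weaker than what a completers-only ANOVA needs. The sample size of 18 raised to 20 needs no change.

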#### Inclusion criteria

Chronic temporomandibular disorders (TMD)Age ≥ 18 yearsProvided written informed consent to participate in the trialPositive response to the question, “Do you have pain in the right side of your face, the left side, or both?” [45]Grade III or IV of the Graduation of Chronic Pain Scale (GCPS) [44]No or stable depression for at least 4 weeks

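### The follow-up rule lets a time effect shared by both arms open before-after tests inside one arm, and nothing limits the evidence for taVNS to a comparison with sham.

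*Protocol article*

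**What the plan says.** The Data analysis section sets out a 2 × 3 design (group by visit). It tests main and interaction effects on the secondary endpoints in a mixed ANOVA, then explores global effects through "appropriate post hoc comparisons between individual conditions (i.e., per group or time point". Correction for multiplicity applies where needed. The same section also describes a model with arm, baseline, time and arm-by-time terms, and promises effect estimates with confidence intervals.

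Two other places put the clinical question without naming sham as the comparator. Secondary outcomes asks whether impairments improve and "whether the observed effects last 4 weeks without stimulation". The Visit 2 section asks "whether the effect of taVNS is sustained or rapidly washed out".

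Other parts are clearly between-arm. The Secondary objectives concern differences between stimulation and sham. The sample size, under Primary outcomes, is set for "intervention (stimulation vs. sham) × time (visit 0, visit 1, visit 2) interaction effects of this size".

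**The concern.** A comparison per time point sets stimulation against sham at one visit. A comparison per group sets visits against each other inside one arm, and that does not separate taVNS from anything that improves both arms.

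Shared improvement is plausible here. Sham patients receive a device, training and a contact after one week, so a placebo response can be expected, and the natural course adds to it. Entry requires "Grade III or IV of the Graduation of Chronic Pain Scale (GCPS", so some regression to the mean is possible as well. That last source is weaker: patients are identified at routine screening and GCPS is measured again at Visit 0.

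A shared improvement shows up as a main effect of time. Because the follow-up rule is not restricted to the interaction, that main effect opens the within-arm tests. With about nine patients per arm, chance alone will often make one arm significant and the other not. A report could then present this as efficacy when the difference between the arms is zero.

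Persistence carries a similar risk. A non-significant Visit 1 to Visit 2 change in nine stimulated patients could be read as a lasting effect when it may only reflect low power.

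**Working it through.** **1. The plan's own figure.** Inputs from Primary outcomes: "assuming an alpha error level of 5%, a power of 95%, and a moderate correlation among repeated measures" of at least 0.5 (0.5 used), two groups, three visits. The effect is one "which we consider to correspond to statistically large effects according to Cohen"; no number is given, so f = 0.40 is assumed. Under G*Power's default convention for a within-between interaction:

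- λ = f² × N × m / (1 − r) = 0.16 × 18 × 3 / 0.5 = 17.28
- df = (2 − 1)(3 − 1) = 2 and (18 − 2)(3 − 1) = 32
- power = 0.953 at N = 18, and 0.924 at N = 16

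This agrees with "a sample size of *n* = 18 is required to detect significant intervention", and 18 / (1 − 0.10) = 20 agrees with the recruitment target. The sample size is tied to the interaction, which is a between-arm quantity.

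**2. One within-arm test.** Take n = 9 per arm (18 completers), no taVNS effect, and the same improvement d in both arms. At r = 0.5 the SD of a change is √(2 × (1 − 0.5)) = 1 outcome SD, so d means the same on either scale. The paired t-test has 8 df and noncentrality d × √9 = 3d. Let p be its two-sided 5% rejection probability. The arms are independent, so *stimulation significant, sham not* has probability p(1 − p), which cannot exceed 25%.

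**3. Adding the ANOVA gate.** I simulated 100,000 trials per row: normal data, r = 0.5, and the shared change reached at Visit 1 and kept at Visit 2. The within-arm test is Visit 0 against Visit 1. The Bonferroni column assumes six within-arm tests (2 arms × 3 visit pairs). Columns C to E give the probability of *stimulation significant, sham not*:

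- A: p, one arm
- B: p(1 − p), no gate
- C: gate opened by time or interaction
- D: as C, with Bonferroni
- E: gate opened by interaction only
- F: rejection rate of the interaction test

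| d (SD, assumed) | A | B | C | D | E | F |
|---|---|---|---|---|---|---|
| 0 | 5.0% | 4.8% | 1.8% | 0.5% | 0.9% | 4.9% |
| 0.3 | 12.5% | 11.0% | 6.5% | 2.1% | 1.3% | 4.9% |
| 0.5 | 26.3% | 19.4% | 15.5% | 6.4% | 1.8% | 4.9% |
| 0.7 | 45.5% | 24.8% | 23.0% | 13.4% | 1.95% | 5.1% |
| 0.8 | 55.9% | 24.7% | 23.7% | 17.7% | 1.8% | 5.0% |
| 1.0 | 74.8% | 18.8% | 18.6% | 23.8% | 1.5% | 4.9% |

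Simulation error is about 0.3 percentage points at the largest values.

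The interaction test is unaffected by the shared change. The misleading pattern comes from letting the time effect open the gate (C against E). Multiplicity correction lowers it for small shared changes but does not remove it (D).

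**4. Persistence.** The formula in step 2 also applies to Visit 1 against Visit 2 in nine stimulated patients. A true loss of 0.5 SD is detected with probability 26%, so it is missed in 74% of trials. A loss of 0.8 SD is missed in 44%. A non-significant change is therefore weak evidence that an effect has lasted.

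**The case against.** The plan's design already handles shared improvement. The trial is randomised against sham, the secondary objectives are between-arm, and the sample size and the model both rest on the arm-by-time interaction. Comparisons per time point are the contrast one would want, and baseline adjustment and confidence intervals are already promised. All of this stands.

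A reader might infer that the plan takes a within-arm change as the taVNS effect, or will judge persistence by a non-significant Visit 1 to Visit 2 test. No sentence says either. The wording only leaves those readings open.

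A reader might also blame selection on severe pain grades. That argument is limited. The ANOVA sentence names the secondary endpoints, whereas GCPS is a primary outcome, so selection on GCPS reaches those endpoints only through correlations the documents do not give. The new GCPS measurement at Visit 0 absorbs part of the effect too. Placebo response and natural course are the stronger reasons to expect shared change.

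The probabilities depend on an assumed shared change and on a reader who ignores the interaction. With no shared change, the gated pattern occurs in about 2%. This is also a feasibility pilot, and the progression indicators in Table 2 are recruitment, retention and compliance, so no post hoc p-value decides whether a larger trial follows.

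Exact contrasts are often left to an analysis plan. Here, though, the article does state a follow-up rule, and that rule is too wide. The objection lowers the weight of the point but does not remove it.

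**Conclusion.** The point holds as a flaw in the follow-up rule. Any global effect, including a time effect shared by both arms, opens within-arm tests, and nothing limits the evidence for taVNS to the interaction or a between-arm contrast. If within-arm results were read alone, a false appearance of efficacy would arise in about 7% to 24% of trials (about 2% to 24% with the assumed Bonferroni correction), against under 2% with an interaction-only gate. These figures assume 9 completers per arm, r = 0.5, no taVNS effect and a shared change of 0.3 to 1.0 SD, which the documents do not supply.

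The stronger conclusion, that the planned test of taVNS is itself invalid or inflated, is not supported: the interaction test rejects in about 5% at every shared change examined. No change to the sample size follows from this point.

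**What to change.** Amend the Data analysis section to state that:

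- evidence for taVNS rests on the group × time interaction and on the baseline-adjusted stimulation-minus-sham differences at Visit 1 and Visit 2, each with a 95% confidence interval;
- persistence is judged by the between-arm difference at Visit 2, not by the absence of a significant change from Visit 1 to Visit 2;
- within-arm changes are reported descriptively, without p-values;
- a main effect of time is not evidence for taVNS.

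Name sham as the comparator where Secondary outcomes and Visit 2 pose the improvement and persistence questions.

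The cost is wording and the loss of within-arm p-values. No extra patients, visits or data are needed, and a model with a baseline term is already planned.
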